### Allocation and Blinding

A deidentified list of eligible participants will be exported from CCO to an independent statistician who will allocate participants to receive 1 of the 8 experimental conditions via simple randomization using computer-generated random numbers.

The different email versions (featuring the different BCTs to be tested) (see Multimedia Appendix 3) will be sent out in 45-minute intervals starting from 9 AM on the 10th day of each month (or if the day falls on the weekend, on the next business day) for 4 months between May and August 2017. The emails could not be sent at the same time since the Cancer Care Ontario’s outgoing mail server could not handle sending out all of the emails at the same time. That is why a delivery schedule made up of 9 intervals (each 45 minutes long) was devised. To address the concern raised regarding sending time, we randomized the order in which the email versions would be sent (ie, 1 version sent per interval) per month. Delivery order will be determined via block randomization. 

**Table 2 table2:** Experimental conditions. + refers to the presence of the factor and – refers to the absence of the factor.

Experimental condition	Factor 1: anticipated regret	Factor 2: material incentive	Factor 3: problem solving
1	–	–	–
2	+	–	–
3	–	+	–
4	–	–	+
5	+	+	–
6	+	–	+
7	–	+	+
8	+	+	+

All randomization procedures will be conducted in SAS version 9.4 (SAS Institute Inc). Treatment allocation will be concealed from the research team and CCO collaborators. It is not possible to blind participants as they must receive the intervention and may notice differences in email content and design; however, they are unlikely to be aware of the different components of the email being tested.

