### Statistical Analyses

Physician baseline characteristics (sex, years of practice), their history of SAR use (previous use/no previous use), their baseline cancer screening rates (breast, cervical, and colon), and their practice characteristics (size of group, rurality, payment model) will be described across experimental conditions.

The unit of analysis for all outcomes will be the primary care physician. The effect of each intervention factor on the primary outcome (accessing the SAR at least once during the 4-month trial) will be analyzed using logistic regression. Indicator variables will be specified for each of the experimental factors using effect coding where +1 indicates the presence and –1 the absence of each factor. With effect coding, the regression coefficient represents the difference in the mean response across all experimental conditions with that factor turned on against the mean for all experimental conditions with that factor turned off. For example, the regression coefficient for “anticipated regret” will represent the difference in the log-odds of accessing the SAR for providers allocated to conditions where this factor is turned on (study arms 2+5+6+8) versus providers allocated conditions where the factor is turned off (study arms 1+3+4+7) (Table 2). The effect of each intervention factor will be expressed as an odds ratio with 95% confidence interval. The model will adjust for history of SAR use as a fixed covariate.

Dichotomous secondary outcomes (participants opting out of emails or with emails that bounce back) will be analyzed as described for the primary outcome. Total number of times the SAR was accessed and number of calls to CCO will be analyzed using Poisson regression with the natural log of the number of person-months as an offset term. For these models, the effect of each intervention factor will be expressed as a rate ratio with 95% confidence interval. In the event of significant overdispersion as assessed by a Lagrange multiplier test, a negative binomial distribution will be specified. For physician adherence to cancer screening guidelines, the dependent variable will be the number of eligible patients who meet a set of cancer-specific guidelines out of the total number of eligible patients listed to that provider and analyzed using logistic regression.

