**Subgroup analyses**		
	History of SAR use	PEM physicians who have never logged in, those who have not logged in for 1 year but did previously, and those with 1 or >1 log-ins in the year prior to the trial
	Baseline cancer screening rate: breast (pretrial)	Proportion of enrolled, eligible patients who are up to date with breast screening at the physician level as of March 31, 2017
	Baseline cancer screening rate: cervical (pretrial)	Proportion of enrolled, eligible patients who are up to date with cervical screening at the physician level as of March 31, 2017
	Baseline cancer screening rate: colon (pretrial)	Proportion of enrolled, eligible patients who are up to date with colorectal tests intended for screening at the physician level as of March 31, 2017
	Sex	Sex of physician
	Years in practice	From the year of graduation
	Practice size	Number of patients enrolled to the physician’s practice
	Size of group	The total number of physicians belonging to the group and practicing within the LHIN^e^ Note: physicians who are part of the physician enrollment model group but practicing in another LHIN will not be included in this count
	Payment model	Identifies the specific type (ie, fee-for-service or capitation)
	Rurality	According to postal code of the PEM physician’s primary practice

^a^SAR: Screening Activity Report.

^b^PEM: physician enrollment model.

^c^FOBT: fecal occult blood test.

^d^CCO: Cancer Care Ontario.

^e^LHIN: Local Health Integration Network.

For testing each experimental factor, a sample size of 5576 physicians achieves 95% power to detect an absolute difference of 4% in SAR use (between those with the factor present versus those with the factor absent) using a 2-sided test at the 5% level of significance assuming a control arm proportion of 0.20 (estimated based on prior CCO data). We would consider small differences in proportions of primary care providers accessing the SAR to be clinically important. For example, if an intervention component resulted in only 4% more primary care providers accessing the SAR (ie, 223 more primary care providers) and if each of those primary care providers identified only a few patients overdue for screening, this would result in cancer screening for an additional 500 to 600 Ontarians.

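### The log-in count model names no covariate, although prior log-in history is collected and the primary model adjusts for it; the rate ratios are valid but less precise than they could be

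*Protocol article*

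**What the plan says.** All references are to the protocol article.

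- **Primary model (Statistical Analyses).** SAR access is analysed by logistic regression on the three factors, and "The model will adjust for history of SAR use as a fixed covariate".
- **Dichotomous secondary outcomes (same section).** Opt-outs and bounced emails follow the primary approach, so they take the adjustment with them.
- **Count outcomes (same section).** Log-ins and calls have their own specification, which begins: "Total number of times the SAR was accessed and number of calls to CCO will be analyzed using Poisson regression with the natural log of"; follow-up in person-months is the logged quantity, entered as an offset. Effects are reported as rate ratios with 95% intervals. The fallback is: "In the event of significant overdispersion as assessed by a Lagrange multiplier test, a negative binomial distribution will be specified". No covariate is mentioned.
- **History of SAR use.** The opening paragraph of Statistical Analyses describes it as a two-level item (previous use or none). Table 3, under subgroup analyses, has finer groups: "PEM physicians who have never logged in, those who have not logged in for 1 year but did previously, and those with 1 or >1", where the last group is defined by use in the pre-trial year.
- **Allocation.** The statistician will "allocate participants to receive 1 of the 8 experimental conditions via simple randomization using computer-generated random numbers", so the design does not balance history across conditions.

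**The concern.** How often a physician logged in before the trial is the natural baseline measure for how often that physician logs in during it. The authors thought it prognostic enough to adjust the yes/no version of this behaviour. They also carry the adjustment to opt-outs and bounced emails, where a link with prior use is less obvious. The count of the same behaviour is left without it.

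If the text is followed literally, predictable differences between never-users and recent users enter the count model as unexplained overdispersion. What is at stake is the precision of the factor rate ratios on the only outcome that measures repeat use of the SAR. The sample size is fixed by registration, so precision cannot be gained by enrolling more physicians.

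**Working it through.** **1. The plan's own figure.** The power statement reads: "a sample size of 5576 physicians achieves 95% power to detect an absolute difference of 4% in SAR use", "using a 2-sided test at the 5% level of significance assuming a control arm proportion of 0.20 (estimated based on prior CCO data"). With 5576/2 = 2788 physicians per factor level, proportions 0.20 and 0.24, and pooled proportion 0.22:

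z = [0.04 × √2788 − 1.96 × √(2 × 0.22 × 0.78)] / √(0.20 × 0.80 + 0.24 × 0.76) = (2.112 − 1.148) / 0.585 = 1.647, so power = 95.0%.

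The stated 95% reproduces and is not in dispute. It concerns the primary outcome. No power or target difference is given for the log-in count.

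**2. Inputs that must be assumed.** The documents give no log-in distribution, no shares of the history groups and no strength of association. Two sets of assumptions were tried, both with N = 5576 and a true rate ratio of 1.20 (the relative size of 0.24 against 0.20).

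**3. First set, by simulation.** Shares are 0.35/0.25/0.20/0.20 (never, lapsed, 1, >1 log-ins), with negative binomial counts and dispersion 1.0 to 2.0. There were 200 trials per scenario for four categories and 120 for yes/no. The variance cut is 1 − (SE adjusted / SE unadjusted)².

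| History effect | Four-month means | SE, none → four categories | Cut | SE, none → yes/no | Cut |
|---|---|---|---|---|---|
| Strong | 0.04, 0.08, 0.35, 1.8 | 0.0722 → 0.0582 | 35% | 0.0722 → 0.0687 | 9% |
| Moderate | 0.10, 0.15, 0.35, 1.0 | 0.0676 → 0.0619 | 16% | 0.0678 → 0.0660 | 5% |
| Weak | 0.18 to 0.60 | 0.0648 → 0.0633 | 5% | 0.0642 → 0.0636 | 2% |

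Simulated power with four categories rises from 72% to 88%, 77% to 85% and 83% to 86%, with Monte Carlo error of about 3 points per figure. With yes/no coding, the normal approximation Φ(ln 1.20 / SE − 1.96) rises by about 4, 2 and 1 points. If Table 3's last group is read as one category (three in all), a strong effect gives a 23% cut. A repeat with 60 trials per scenario gave cuts of 31%, 16% and 5% (four categories) and 9%, 6% and 2% (yes/no).

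**4. Second set, in closed form.** Shares w are 0.40/0.30/0.15/0.15, with stratum means m and within-stratum dispersion k. For factor on versus off:

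- SE adjusted = 2 / √[N × Σ w m / (1 + k m)]
- SE unadjusted = 2 / √[N × μ / (1 + K μ)], where μ is the overall mean and K = (marginal variance − μ) / μ²

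Moderate case, m = 0.08, 0.15, 0.40, 1.2 and k = 1:

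- μ = 0.032 + 0.045 + 0.060 + 0.180 = 0.317
- Marginal variance = 0.317 + 0.249 + 0.149 = 0.715, so K = 3.96
- SE unadjusted = 2 / √(5576 × 0.1405) = 0.0714
- SE adjusted = 2 / √(5576 × 0.1934) = 0.0609
- Variance ratio 1.38, so the cut is 1 − 1/1.38 = 28%; power 72% → 85%

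The weak case (means 0.20 to 0.60) gives ratio 1.06, cut 6%, power 88% → 90%. The strong case (0.03 to 1.6, k = 0.7) gives ratio 1.59, cut 37%, power 66% → 85%. The implied proportions with any log-in are 22.6% (weak), 19.3% (moderate) and 17.7% (strong), close to the plan's 0.20.

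**5. Bias.** In simulations of the second set the estimated rate ratio was about 1.19 with and without history. Adjustment changes precision, not the target.

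**The case against.** The strongest reply is that this rests on silence. The document is a journal article, its analysis plan is not shown, and covariates for a secondary outcome are often left to that plan. The count sentences do not repeat the effect coding either, and nobody would infer that it was dropped. The text does not rule out adjustment. This limits the point but does not remove it. The article fixes this model down to its offset and overdispersion test, and carries the primary approach over only to other outcomes, so a literal reading gives an unadjusted model.

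The reply on size also stands. Every input behind the gain is assumed, and on the two-level definition in Statistical Analyses the gain is small.

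A reader might infer more than the documents support:

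- **That the estimate is biased or invalid.** It is not; physicians are randomised.
- **That a definite amount of power is lost.** No document figure supports one.
- **That the negative binomial switch adds a further loss.** It is the correct guard against intervals that are too narrow, and it is where the whole loss shows. In the strong case of the first set, the model-based Poisson SEs were 0.0394 and 0.0395 with and without history.
- **That the count and primary results become non-comparable.** An odds ratio for any access and a rate ratio for counts differ whatever the adjustment.
- **That this is a key outcome.** The article calls it only secondary.

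Subgroup analyses by history of SAR use are planned, but they do not adjust the main count estimate.

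**Conclusion.** The point holds as a matter of efficiency on a secondary outcome. As written, the log-in count model leaves out a collected baseline measure of the same behaviour that the primary model uses.

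The direction of the loss was the same in every scenario tried; its size is not known. It depends on how strongly prior use predicts log-ins and on how history is coded. The variance reduction is about 2-9% for previous use yes/no, which was checked on the first set of inputs only. It is about 5-35% for the finer Table 3 categories (6-37% on the second set). With a weak association the power gain is 2 to 3 points, within simulation error. Most of the possible benefit comes from separating recent and repeat users from lapsed ones, so simply copying the two-level covariate into the count model would recover little.

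**What to change.** Add to the count-model paragraph that the log-in count model will include history of SAR use as a fixed covariate with four levels: never; not in the past year but earlier; one log-in in the past year; more than one. State that the Lagrange multiplier test is applied to this adjusted model.

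State a single definition of history of SAR use for both the primary and the count model, since Statistical Analyses and Table 3 now differ. Make clear that Table 3's last group is split into one and more than one log-in. Nothing here requires a change to the model for calls.

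The cost is one or two sentences, three indicator variables among 5576 physicians, and no new data. The article reports that analysis had not begun at submission, so the covariate could be fixed without knowledge of results. Added after the results are seen, it would be open to challenge.

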We had no a priori hypotheses about the interactions between the BCTs tested (anticipated regret, material incentive [behavior], and problem solving). Secondary analyses will include all 2-way interaction terms between experimental factors as well as comparison across the 8 experimental conditions. Secondary analyses will examine differences across subgroups defined by physician characteristics (eg, sex, years in practice, baseline screening rates, practice size, history of SAR use) and practice characteristics (eg, size of group, rurality, payment model). The length of the emails will also be explored as a potential effect modifier.

All analyses will be conducted in SAS version 9.4 (SAS Institute Inc) with statistical significance assessed at the 5% level.

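### The three secondary screening-adherence outcomes are modelled by events/trials logistic regression with no allowance for between-physician variation, so their standard errors are too small by a factor that depends on practice size and ICC

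*Protocol article*

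**What the plan says.** All statements are in the protocol article.

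- **Randomisation** (Allocation and Blinding): a statistician will "allocate participants to receive 1 of the 8 experimental conditions via simple randomization using computer-generated random numbers". The participants are physicians.
- **Unit of analysis** (Statistical Analyses): "The unit of analysis for all outcomes will be the primary care physician".
- **Adherence outcomes** (Statistical Analyses): the dependent variable is "the number of eligible patients who meet a set of cancer-specific guidelines out of the total number of eligible patients" on the physician's list, that is, the "total number of eligible patients listed to that provider and analyzed using logistic regression". Table 3 defines a numerator and a denominator per physician for each of the three cancers.
- **Overdispersion** (Statistical Analyses): "In the event of significant overdispersion as assessed by a Lagrange multiplier test, a negative binomial distribution will be specified". This follows the Poisson models for number of SAR accesses and number of calls. No random effect, robust variance, beta-binomial model or scale parameter is named for adherence.
- **Covariates**: the only adjustment named is history of SAR use, in the description of the primary model. Baseline screening rates are to be described and used for subgroups.
- **Significance**: all analyses are conducted "with statistical significance assessed at the 5% level".

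**The concern.** A logistic model for events out of trials takes its variance from the binomial distribution. It treats each patient as an independent observation, given the covariates. Putting the data in one row per physician changes nothing, because the grouped likelihood gives the same estimates and standard errors as patient-level records.

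The email version is assigned to the physician. If physicians differ in their screening rates for reasons outside the model, the information about a factor effect is limited by the 5576 physicians and not by the total number of their patients. The article's own rationale implies such differences. It calls provider behaviour an important determinant of screening, the SAR compares each physician with a regional average, and baseline screening rate is a planned subgroup variable.

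The negative binomial fallback cannot repair this. It is an alternative to the Poisson distribution for counts, not to the binomial for proportions.

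Adherence is the outcome that connects log-ins with patients, and the Introduction names screening rates as the ultimate aim. With intervals that are too short, an email component with no effect on screening could be reported as raising or lowering it.

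**Working it through.** **Step 1: the plan's own figure.** The article gives no power or precision figure for adherence. Its only power statement concerns the primary outcome: "a sample size of 5576 physicians achieves 95% power to detect an absolute difference of 4% in SAR use", "using a 2-sided test at the 5% level of significance assuming a control arm proportion of 0.20". With 5576 / 2 = 2788 physicians per factor level, 0.20 versus 0.24 and two-sided 5%:

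- SE under the null = sqrt(2 × 0.22 × 0.78 / 2788) = 0.01110
- SE under the alternative = sqrt((0.20 × 0.80 + 0.24 × 0.76) / 2788) = 0.01108
- power = Φ((0.04 − 1.96 × 0.01110) / 0.01108) = Φ(1.65) = 0.950

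The stated 95% reproduces. This outcome is one yes/no value per physician, so no patient clustering enters.

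**Step 2: inputs for adherence.**

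- Number randomised: 5576 physicians (article).
- Eligible patients per physician, m: not given. Assumed 100 to 300.
- ICC (between-physician variation left after the model's covariates): not given. Assumed 0.01 to 0.10.
- Mean adherence: assumed 0.60. The Introduction says that more than one-third are not up to date, so the rate is below about 0.67.

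To give the ICC a meaning, the between-physician SD of the true rate is sqrt(ICC × 0.60 × 0.40). This is 4.9 percentage points at ICC 0.01, 6.9 at 0.02, 11.0 at 0.05 and 15.5 at 0.10.

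**Step 3: formulas.** Design effect DE = 1 + (m − 1) × ICC. True SE / model SE = sqrt(DE). Actual type I error of a nominal 5% test = 2 × (1 − Φ(1.96 / sqrt(DE))).

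Example, m = 200 and ICC 0.02: DE = 1 + 199 × 0.02 = 4.98; sqrt(DE) = 2.23; 1.96 / 2.23 = 0.88; type I error = 38%.

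| m | ICC | DE | SE too small by factor | Actual type I error |
|---|---|---|---|---|
| 100 | 0.01 | 1.99 | 1.41 | 16.5% |
| 100 | 0.02 | 2.98 | 1.73 | 26% |
| 100 | 0.05 | 5.95 | 2.44 | 42% |
| 200 | 0.02 | 4.98 | 2.23 | 38% |
| 200 | 0.05 | 10.95 | 3.31 | 55% |
| 300 | 0.01 | 3.99 | 2.00 | 33% |
| 300 | 0.02 | 6.98 | 2.64 | 46% |
| 300 | 0.05 | 15.95 | 3.99 | 62% |
| 300 | 0.10 | 30.90 | 5.56 | 72% |

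Outside the assumed range, m = 50 with ICC 0.005 still gives a factor of 1.12 and a type I error of 7.9%. The direction is the same for every positive ICC; only the size changes.

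**Step 4: check by simulation.** The set-up was 5576 physicians, three ±1 factors with no effect, beta-binomial patient counts, unequal practice sizes and 300 replicates per setting. The grouped logistic model rejected in 19% (m = 100, ICC 0.01), 49% (100, 0.05), 44% (200, 0.02), 58% (200, 0.05), 66% (300, 0.05) and 76% (300, 0.10). These figures are somewhat above the formula because practice sizes vary.

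**Step 5: effect of a physician-level variance.** In a second simulation (400 runs, m = 200), the plain model rejected in 41% (ICC 0.02) and 59% (ICC 0.05). Physician-level sandwich standard errors brought this to 7.5% and 5.0%. The simulation error at 5% is about sqrt(0.05 × 0.95 / 400) = 1.1 points, so this confirms the correction only roughly. In the simulation of Step 4, scaling by the Pearson statistic gave about 6% to 8%.

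**The case against.** **The article is condensed, and variance options often stand in the analysis plan.** The text does not say that a scale parameter or robust variance is excluded. This carries some weight, but it does not settle the matter. The article fixes both the dependent variable and the model, and for the neighbouring count outcomes it goes down to the test for overdispersion and the fallback distribution. An analyst who follows the adherence sentence as it stands gets the binomial variance.

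**The physician is declared the unit of analysis.** A reader might infer that this sentence cures the problem, or that the plan contradicts itself. Neither follows. One events/trials row per physician is compatible with the sentence, and so are outcomes defined at physician level. The sentence suggests that physician-level inference was intended, but it does not supply the variance that such inference needs.

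**The size is unknown.** This stands. A reader might infer that the intervals will be several times too narrow. The documents do not support that as a fact, because they give neither patients per physician nor an ICC. At m = 100 and ICC 0.01 the factor is 1.4.

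**Nine tests.** With three factors and three cancers, a reader might also infer that at least one spurious finding is more likely than not. That calculation needs the nine tests to be independent, and the three cancers are measured in the same practices. Moreover, nine valid independent 5% tests would already give 1 − 0.95^9 = 37%, so part of that figure is multiplicity and not this defect.

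**Only secondary outcomes are affected.** This also stands. The stated objective is log-ins, and the power calculation concerns SAR use only.

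**Conclusion.** The concern holds for the three adherence outcomes. The rule as written gives standard errors that are too small and a type I error above 5% whenever physicians differ in screening rates beyond what the covariates explain. It is a wrongly fixed analysis and not a missing detail.

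The size rests on assumed values. For 100 to 300 eligible patients per physician, standard errors are understated by about 1.7 to 4.0 at ICC 0.02 to 0.05, and by 1.4 at the mildest setting in the table. The actual type I error runs from about 16% to 72% over ICC 0.01 to 0.10.

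The primary analysis and its power statement are sound on this point. The trial's main question about log-ins does not depend on the correction; any claim about screening rates does.

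**What to change.** Replace the model statement for adherence with: 'analysed by events/trials logistic regression with physician-level robust (GEE sandwich) standard errors, for all three cancers and without a preliminary overdispersion test'.

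One method should be named, because the alternatives do not all estimate the same quantity. A physician random intercept gives a physician-specific odds ratio, whereas the sandwich approach keeps the population-averaged odds ratio of the model now planned. With one row per physician, the point estimates stay as they are and only the standard errors change. The preliminary test is dropped because between-physician variation is to be expected by design.

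The cost is one sentence in the analysis section and a small change to the SAS code. No new data are needed, and the article's Results section says that data cleaning and analysis had not begun. The downside is wider confidence intervals, by roughly the factors in the table, but these intervals are valid.
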